##### Data collection methods and experimental procedure

##### Pre-intervention examination of the study population:

A structured questionnaire will be used to collect demographic data of all the study participants. In-depth interviews of five farmers in each village will be done to study human perceptions of the disease. Structured observations will be done in all selected households to study practices related to the transmission of the disease such as pig rearing practices, use and status of latrine, boiling of water for drinking, washing hands before eating and after using a latrine, and eating of infected pig meat.

All pigs in the household will be examined by the researcher using lingual palpation and blood samples collected for antigen ELISA.

# Allocation of villages to intervention:

Two groups will be compared whereby one group will receive the health education while the other group will act as a control. The villages will be grouped according to their similarities in their prevalence of porcine cysticercosis obtained during pre-intervention study and randomised within groups to either control or intervention.

Intervention:

Participants in the control group will follow their usual hygiene and pig management practices. For the intervention group, the educator in each village will organise and conduct two training sessions one- month interval. After the first session the educator will distribute pamphlets to the participants for further reference. The day after the session, the participants in the intervention group will watch a video program. The researcher will participate in the sessions as an audience, therefore the interventions in the selected villages will be planned such that the researcher will participate in all the villages.

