**Study population**

Sample size calculation:

Although the village will be the unit of intervention allocation, the main analysis will be based on individuals since from previous study there was little variation in the prevalence of porcine cysticercosis in different villages (coefficient of variation was about 0.1). Therefore the sample size has been calculated using the formula,

n = [(z1 + z2)2 2P (1-P)]/(p1 – p2)2.

In the formula, n is number of pigs required in each group, z1 is the z score for the specified confidence level, and z2 is the z score for the specified power. p1 and p2 are the prevalence of the disease in the intervention and control group respectively, and p1 and p2 P is the average of p1 and p2 (Smith and Morrow, 1996).

The sample size is calculated based on the prevalence of porcine cysticercosis as the main outcome measure. The prevalence of porcine cysticercosis in the area was estimated to be 14.64% adjusted for various confounders ([name], 1999). We would like the present study to have 80% power to detect a significant difference with 95% confidence if the intervention will reduce the prevalence of porcine cysticercosis by 30%. The number of villages required in each group is therefore calculated to be:

n = [(1.96 + 0.84) 2 2 x 0.1244 (1-0.1244)]/(0.1464-0.1023)2

= 878.20.

Approximately 900 pigs will be examined in each of the two groups. A total of 1800 pigs will be examined before intervention and 1800 after intervention.

Selection of villages and study participants:

The number of villages to be included in the study will depend on the number of pig farmers available in the villages. This information will be obtained in the pilot study. All pig farmers in the selected villages will be enrolled in the study.

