# Post-intervention examination of the study population:

The researcher will reassess perceptions and practices immediately after the intervention and at the end of the study. All pigs born after the intervention will be examined. Similar methods of data collection used in the pre-intervention study will be used in this study. However, the last questionnaire interview will include a question designed to investigate if the participants in the control group have received any information regarding the health education from the intervention group in order to take care for possible confounder during data analysis. The research will also investigate if there has been any change in hygiene policy at any time during the study.

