**Study limitations**

Due to the short period available for the data collection (about two years), it might not be possible to observe significant reduction in the disease prevalence. However, improvement in perceptions and practices related to the transmission of the disease will be used as intermediate outcomes to indicate reduction in the transmission of the disease.

Maternal antibodies due against porcine cysticercosis have been reported to persist beyond nine months of pig’s life. This may limit the use of ELISA or immunoblot tests that have been reported to respond on these antibodies. This is because we would like to detect actual cases (and not false positives due to maternal antibodies) and to be able to disentangle cases hat occured before and those that occurred after the intervention. Most studies on antigen ELISA for porcine cysticercosis are still under trial and some have reported that antigens are detected up to 200 days post-infection and tend to disappear afterwards probably due to formation of immune complexes.

We are not sure that we will get enough pigs for post-intervention study since we don’t know how prolific are the pigs in the study area. From the previous study, one farmer in Mbulu had an average of 1.8 pigs. Our aim is to examine a different population of pigs in the post-intervention from the pre-intervention study. This is because in this particular disease we cannot know the onset of the infection, otherwise we could include the pre-intervention population that had not been infected in the post-intervention study.

Due to the fact that the intervention is information based, leaking of information from intervention to the control group might be a problem. However care will be taken to have a clear geographical separation of the groups. In addition, participants in the control group will be assured well in advance that they will receive the intervention after the study in order to minimise chances of them seeking information from the intervention group. The researcher will investigate if there is any leakage of information from the intervention to the control group, or if there is any change in hygiene policy during the study period in order to take care of these during data analysis. [In this point I am still thinking if we can use blinding which is known to reduce bias]

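### The researcher attends the sessions in every intervention village and also measures the outcomes, so the examiner cannot be masked, and blinding is left undecided

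*Protocol*

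**What the plan says.** Four places in the Protocol bear on this.

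- Intervention, under Allocation of villages to intervention: "The researcher will participate in the sessions as an audience". The same sentence has the interventions scheduled so that she can be present in all the villages that receive them.
- Pre-intervention examination of the study population: "All pigs in the household will be examined by the researcher using lingual palpation and blood samples collected for antigen ELISA".
- Post-intervention examination of the study population: "The researcher will reassess perceptions and practices immediately after the intervention and at the end of the study". Pigs born after the intervention are examined, and data collection is to use methods similar to those at baseline. No other examiner is named.
- Study limitations, in a bracketed remark: "I am still thinking if we can use blinding which is known to reduce bias". No masking is specified anywhere else.

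The Introduction describes tongue examination as detecting up to 70% of infected pigs with 100% specificity, and as weaker in early or light infection. Study limitations says that perceptions and practices will serve as intermediate outcomes, because a fall in prevalence may not be seen in the time available.

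**The concern.** Lingual palpation depends on how carefully the examiner searches, and practice observations and perception interviews depend on how they are scored. An examiner who has sat through the sessions knows the arm of every village before follow-up. If that knowledge changes search effort or scoring even slightly, the change enters the between-group difference directly.

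The planned analysis cannot separate this from a real effect. Villages are allocated after the baseline examination, so arm-dependent detection can arise only at follow-up. Adjusting for baseline values, pig and household covariates and clustering leaves it in place, and more pigs would not reduce it. Both routes to a positive conclusion are exposed: the prevalence result, and the practice and perception results that the Protocol falls back on.

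**Working it through.** **Who knows what, and when.** Allocation follows the baseline survey, so baseline palpation is done before any arm exists. The sessions come next, and the researcher is at all of them. Every later measurement assigned to her, or inferred to be hers, is made with the arm known. The attendance rule and the open thought about blinding cannot both stand for the same examiner.

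**The plan's own figure.** From Study population: "n = [(1.96 + 0.84) 2 2 x 0.1244 (1-0.1244)]/(0.1464-0.1023)2". This is 7.84 × 2 × 0.1244 × 0.8756 / 0.0441² = 878.20, which matches the stated value and is rounded up to about 900 per group. The sample size itself is not affected by this point. At 900 per group the planned effect is 900 × 0.1464 = 131.8 positives against 900 × 0.1023 = 92.1, a difference of about 40 pigs.

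**Illustration of the size of bias.** Inputs:

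- Control prevalence 14.64% and about 900 pigs per group, from Study population. The earlier Mbulu survey described in the Introduction used lingual examination, so I treat 14.64% as prevalence as seen by palpation.
- Specificity 100%, from the Introduction. Apparent prevalence is then true prevalence times sensitivity, so only the ratio of sensitivities between arms matters and the 70% cancels. For example, 70% falling to 63% is a 10% relative loss.
- Relative loss of detection r in the intervention arm. This is **an assumption**; the documents give no value.

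With no true effect, p_I = 0.1464 × (1 − r), shift = 0.1464 × r, SE = √{[0.1464 × 0.8536 + p_I(1 − p_I)]/900}, and the chance of a false significant benefit is Φ(shift/SE − 1.96). The last column divides shift/SE by √2, an assumed design effect of 2, to show the direction in which clustering acts.

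| Assumed r | Positives lost per 900 | Share of a 30% reduction | Shift | SE | Shift/SE | False benefit, no clustering | False benefit, design effect 2 |
|---|---|---|---|---|---|---|---|
| 0 | 0 | 0 | 0 | 0.0167 | 0 | 2.5% | 2.5% |
| 2% | 2.6 | 7% | 0.0029 | 0.0166 | 0.18 | 3.7% | 3% |
| 5% | 6.6 | 17% | 0.0073 | 0.0165 | 0.44 | 6.5% | 5% |
| 10% | 13.2 | 33% | 0.0146 | 0.0163 | 0.90 | 14.4% | 9% |
| 15% | 19.8 | 50% | 0.0220 | 0.0161 | 1.36 | 27.5% | 16% |

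Small gaps do little. Gaps of 10% or more matter, and 10% corresponds to missing about 13 positive pigs out of roughly 132.

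**The case against.** The strongest reply is that the size of the bias is not in the documents. Both r and its direction are assumed: a wary examiner might search harder in intervention pigs, which would work against the intervention. The unclustered rates also use a simpler analysis than the hierarchical logistic model in Statistical analysis, so they lie at the upper end. All of this stands. A reader might infer that examiner bias will supply a sizeable part of the 30% effect, or that 14.4% or 27.5% is this trial's error rate. The documents support neither.

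Three further limits also stand.

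- A reader might take it as written that the researcher palpates the follow-up pigs. The post-intervention section uses the passive. That she does so is a reasonable inference from the baseline section and the instruction to use similar methods.
- A reader might count her training of the village educators as further unmasking. Phase one has an educator trained in each study village, before allocation, so that step does not reveal the arm.
- Blinding has been raised and left undecided; it has not been rejected.

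It can also be said that the planned blood samples are a second, more objective measurement. That is partly right, but the Protocol does not say that they are read masked. Study limitations also describes antigen ELISA as largely still under trial, with antigen tending to disappear after about 200 days. The blood can test the palpation result but cannot replace it, and it does nothing for the practice and perception ratings.

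**Conclusion.** The point holds as a design weakness. As written, the person who measures the outcomes is certain to know every village's arm, and the planned model cannot distinguish differential detection or scoring at follow-up from an intervention effect. This rests on the attendance rule, which is explicit, on the reassessment of perceptions and practices, which is explicit, and on follow-up palpation by the same person, which is inferred.

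The size is unknown. Over assumed relative losses of 2% to 15%, the one-sided false-benefit rate would run from about 3.7% to 27.5% without clustering, and from about 3% to 16% at an assumed design effect of 2. The case for change is that exposure to this bias is certain as the plan stands and is cheap to reduce; it does not depend on any particular value in that range.

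**What to change.** 1. Code the blood samples already planned, so that the antigen ELISA is run and read without knowledge of village or group. Report it as a masked check on palpation, not as a replacement, and state the assay limits given under Study limitations.
2. Remove the rule that the researcher attends the sessions. Let another member of the budgeted team, such as the technician, observe delivery and not disclose allocation. Withhold the allocation from the researcher until follow-up palpation is done, and palpate before asking the last questionnaire's question about information leaking to controls, since that question reveals the arm. State explicitly who palpates at follow-up.
3. Replace the bracketed remark under Study limitations with this decision. Say there that practice and perception ratings can be only partly masked and will be interpreted accordingly.

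**Cost:** labelling of samples and a change of roles within the team already in the Budget, with no extra staff. The researcher no longer sees delivery at first hand. Field masking may fail, because a colleague in the same small team knows the arms, because the interviews immediately after the intervention may reveal them, and because new latrines or pig housing can show where education was given. Partial masking is still better than an examiner who is certain to know.

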# Post-intervention examination of the study population:

The researcher will reassess perceptions and practices immediately after the intervention and at the end of the study. All pigs born after the intervention will be examined. Similar methods of data collection used in the pre-intervention study will be used in this study. However, the last questionnaire interview will include a question designed to investigate if the participants in the control group have received any information regarding the health education from the intervention group in order to take care for possible confounder during data analysis. The research will also investigate if there has been any change in hygiene policy at any time during the study.

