**Statistical analysis**

Due to the fact that pigs will be clustered in households that are also clustered in villages and climates, a hierarchical logistic regression model will be used to analyse the data in order to take care of different levels of clustering and possible interactions. The effectiveness of intervention in improving human perceptions and practices will be computed by comparing average scores in the two groups adjusted for baseline values. Change in the prevalence of porcine cysticercosis will be computed and adjusted for important confounders such as age, sex of the pig, and other important household characteristics that might affect the prevalence of the disease. Seasonal prevalence of porcine cysticercosis will be taken into considerations when evaluating the intervention.

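### Leakage of information to control households is treated as a confounder, and the household covariates in the prevalence model are not limited to pre-intervention values

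*Protocol*

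**What the plan says.** **Timing of allocation.** Under *Allocation of villages to intervention*, villages are grouped by the prevalence found in the pre-intervention survey and "randomised within groups to either control or intervention". Anything that follows from the teaching therefore comes after allocation.

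**Leakage.** Under *Post-intervention examination of the study population*, the last questionnaire asks whether control participants "have received any information regarding the health education from the intervention group in order to take care for possible confounder during data analysis". *Study limitations* returns to leakage, together with any change in hygiene policy, and says both will be investigated "in order to take care of these during data analysis". Neither section names a method.

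**Covariates for prevalence.** Under *Statistical analysis*, the change in prevalence is adjusted for confounders. These are the age and sex of the pig and "other important household characteristics that might affect the prevalence of the disease". The household characteristics are not listed and no time of measurement is given. The same section does specify baseline adjustment for the perception and practice scores.

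**What the education is meant to change.** *Phase two* puts the emphasis on latrines, hand washing, pig housing and indoor feeding. Household practices are observed before the intervention (*Pre-intervention examination of the study population*) and again afterwards by similar methods. *Study limitations* treats improved practices as intermediate outcomes.

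**The concern.** A confounder is a cause of the outcome that is also associated with allocation for reasons other than allocation itself. Leakage does not qualify. It exists because some villages were taught and others were not, and the variable is defined in one arm only. A model term for it, or an exclusion based on it, sets all intervention households against those controls who did not hear, or did not report hearing, about the education. Households that pick up information may differ in risk from those that do not, and randomisation no longer protects that contrast.

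The household covariates raise a related problem. The stated rule for choosing them is that they might affect prevalence. Latrine use and pig confinement after the intervention meet that rule, and they are also the route by which the education is supposed to work. Conditioning on them would estimate only the part of the effect that bypasses them.

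Prevalence of porcine cysticercosis is the main outcome. If either step entered its primary analysis, the estimate would depend on covariate choices made after the data are in, and no longer on the randomisation alone.

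**Working it through.** **1. The plan's own figures.** Under *Study population* the trial is to have "80% power to detect a significant difference with 95% confidence", with control prevalence 0.1464 and intervention prevalence 0.1023:

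n = (1.96 + 0.84)² × 2 × 0.1244 × (1 − 0.1244) / (0.1464 − 0.1023)² = 7.84 × 0.21785 / 0.0019448 = 878.2.

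This matches the stated 878.20. The target difference is 0.1464 − 0.1023 = 0.0441, or 4.4 points, a relative reduction of 0.0441/0.1464 = 30.1%. Power at 900 per group is 81%, ignoring clustering. Nothing in this point changes these figures.

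**2. Dropping informed controls.** The protocol gives neither a leakage rate nor the risk of informed households, so both are assumed. Let a fraction f of controls be informed, with prevalence q among them, and let overall control prevalence be 0.1464. The remaining controls have prevalence x, where f·q + (1 − f)·x = 0.1464. The shift is therefore

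x − 0.1464 = [f / (1 − f)] × (0.1464 − q).

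| f | q = 10% | q = 18% |
|---|---|---|
| 10% | +0.5 points | −0.4 points |
| 20% | +1.2 points | −0.8 points |
| 30% | +2.0 points | −1.4 points |

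For f = 20%: (0.1464 − 0.020)/0.8 = 0.1580 and (0.1464 − 0.036)/0.8 = 0.1380. The shifts are 0.0116/0.0441 = 26% and 0.0084/0.0441 = 19% of the planned difference, in opposite directions. Suppose the information did nothing for those it reached and the intervention arm is at 10.23%. The apparent relative reduction is then 1 − 0.1023/0.1580 = 35.3% or 1 − 0.1023/0.1380 = 25.9%, instead of 30.1%.

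**3. What leakage does to the as-randomised comparison.** Assume that leakage has the full effect in those it reaches. Control prevalence becomes 0.1464 − 0.0441·f.

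| f | Difference | Relative reduction | Power at 900 per group, clustering ignored |
|---|---|---|---|
| 0 | 4.41 points | 30.1% | 81% |
| 10% | 3.97 points | 28.0% | 73% |
| 20% | 3.53 points | 25.6% | 63% |
| 30% | 3.09 points | 23.2% | 53% |

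**4. Adjusting for a practice on the causal path.** The unadjusted odds ratio implied by the plan is (0.1023/0.8977)/(0.1464/0.8536) = 0.66. A simulation of 4 million records per scenario assumed a practice followed by 6% of control and 50% of intervention households. (In the survey cited in the *Introduction*, 94.4% of respondents let their pigs roam, so 5.6% did not.) The practice carried a chosen share of the effect on the log risk ratio scale. The intervention odds ratio after logistic adjustment for it was:

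| Share of effect carried by the practice | Adjusted odds ratio |
|---|---|
| 0 | 0.67 |
| 50% | 0.82 |
| 80% | 0.92 |
| 100% | 1.00 |

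A covariate that carries none of the effect does no harm. One that carries all of it removes the effect entirely. The 50% uptake and the shares are assumptions.

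**The case against.** The case against has four parts.

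- **No method is stated for leakage.** A purely descriptive or sensitivity use would fit the text and be harmless. The design also tackles leakage first, through geographical separation and the promise of later education to controls. This stands, and it makes the bias conditional. It does not rescue the label: calling something a confounder to be dealt with in the analysis ordinarily means adjusting, stratifying or excluding.

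- **The household characteristics are unnamed.** A reader might infer that the protocol commits to adjusting for latrines and pig housing after the intervention and so adjusts its own effect away. The text does not support that. *Statistical analysis* names no such variable, the pre-intervention survey supplies legitimate values, and practices are analysed as outcomes in their own right. Listing covariates can also be left to a statistical analysis plan, so the missing list is no fault. What remains is the rule that is stated: it selects on effect on prevalence and so admits variables on the causal path.

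- **The direction of bias.** A reader might infer that handling leakage inflates the effect. That requires informed controls to be lower-risk households, and the documents do not say who would be informed. The sign is unknown.

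- **Exclusion might correct dilution.** If the education works, part of any shift after removing informed controls undoes real contamination. This is true, but lower prevalence among informed controls could come from the information or from who they are, and the leakage question alone cannot separate the two. That is a reason to show such a result as a sensitivity analysis and not as the primary one.

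**Conclusion.** The point holds in two parts of unequal strength.

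The leakage part is an error in what the protocol states. Contamination that follows from allocation and is recorded only in controls is named a confounder. Using it as one in the main analysis would bias the randomised comparison in a direction that cannot be known beforehand. With 10% to 30% of controls informed and prevalence of 10% or 18% among them, excluding them shifts control prevalence by between +2.0 and −1.4 points, against a planned difference of 4.4.

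The household part is a rule that is too wide, not a commitment to a biased model. It allows post-intervention practices into the prevalence analysis. If one carried 50% to 100% of the effect, the odds ratio would move from about 0.66 to between 0.82 and 1.00.

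All these sizes rest on assumed leakage rates, risks and mediation shares, and the power figures ignore clustering. The stated sample size is not affected. Change in hygiene policy may be an external event and is not part of this conclusion.

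**What to change.** State in *Statistical analysis* that:

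- the primary prevalence analysis compares all villages and households as randomised, whatever the leakage answers show;
- its covariates are limited to the randomisation group or village baseline prevalence, the age and sex of the pig, and household characteristics measured at the pre-intervention survey;
- leakage answers and post-intervention practices are used only in labelled secondary analyses: description, sensitivity or mediation.

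In *Post-intervention examination of the study population* and *Study limitations*, call leakage contamination instead of a confounder. The leakage question need not be put to the intervention arm, which receives the education by design.

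The cost is a few sentences, with no new data and no change to the number of pigs. The price is that the as-randomised estimate is diluted by any real leakage. Under the full-effect assumption with 20% of controls reached, the relative reduction falls from 30.1% to 25.6% and power from 81% to 63%, ignoring clustering. The report should give the leakage rate beside the primary result so that readers can judge the dilution.
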